**Methods:**

This is a two-arm randomized intervention trial. We will recruit 380 participants who meet the following eligibility criteria: 18-29 years of age, own a smartphone running an Android-based operating system, have the WhatsApp messaging app, live in Swaziland, and can adequately grant informed consent. Participants will be allocated into a smartphone interactive, educational story game, and a wait-list control group in a 1:1 allocation ratio. Subsequently, a self-administered Web-based questionnaire will be issued at baseline and after 4 weeks of exposure to the game. We hypothesize that the change in HIV risk perception between pre- and post-intervention assessment is greater in the intervention group compared with the change in the control group. Our primary hypothesis is based on the assumption that increased perceived risk of HIV provides cues to engage in protective behavior. Our primary outcome measure is HIV risk perceived mean change between pre- and post-intervention compared with the mean change in the wait-list control group at 4-weeks post-intervention. We will use standardized regression coefficients to calculate the effect of the intervention on our primary outcome with *P* values. We will conduct both intention to treat and as treated analysis.

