The goal of the game is to maintain relationships with the characters, while staying healthy and happy. Once all the interactions with the characters have been completed, the game will give feedback on choices made and the risks those choices might carry. The game is expected to have an immense appeal to the youth, as an exciting new way to use their smartphones (see Figure 2 for the actual SwaziYolo screenshots). Participants in the wait-list control condition will complete the baseline and the immediate posttest measures as those in the SwaziYolo intervention condition, but will not play the game until the post-intervention assessment.

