#### Four-Weeks Follow-Up Data Collection

Trial participants will be followed-up for 4 weeks, the game will collect log data and send this data to our servers when the participant goes on the Internet, this will allow us to assess the exposure to the intervention without over burdening our participants to manually send us their usage data. Data captured will be limited to login data. In addition to this, a Web-based questionnaire will be sent to participants at the end of the follow-up period. Participants who will miss their 4-week follow-up assessment will be actively traced though phone calls and text messages.

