### Data Management and Statistical Analysis

#### Data Quality Assurance

First, Web-based questionnaires must be usable even for less experienced and knowledgeable Internet users [31], therefore we will exploit specific technical possibilities offered by open source Web-based questionnaires, such as visually highlighting buttons and predefined input fields. Additionally, we will use help features and input checks to assist participants when filling out the Web-based questionnaire. Beyond this, we will pilot test all filters and instructions given in the questionnaire. Second, to limit undesired multiple participation [32], either at baseline assessment or follow-up assessment, “sessions” will be used together with a verification code that participants will receive upon giving informed consent. Third, a specific problem that is faced by Web-based surveys is that respondents may “click through” the questionnaire, a phenomenon that becomes apparent when the interview is completed in less than the theoretical minimum time [31], therefore, the responses will be checked for plausibility and consistency and inconsistent records will be documented and censored from the final analysis.

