#### Primary Outcome Measure: HIV Risk Perception Score

First, we will use bivariate analysis to calculate the mean between baselines and follow-up. Next, to estimate the difference between the 2 groups, we will calculate the difference between the mean change of the intervention group and the mean change of the wait-list control group using two-sample paired *t* test. We will not perform interim analysis.

Secondly, in the case that, even after randomization, we observe some baseline differences, we will use multiple linear regression to adjust for those differences; where the outcome will be the follow-up score and the independent variables will be the intervention group, baseline scores, age, gender, marital status, level of education employment status, current monthly income, and number of times players played SwaziYolo. We will present our results in standardized regression coefficients for the intervention effect on the outcome variable as previously done for this type of hypothesis [25].

Although great effort will be put to minimize attrition, it is common for eHealth trials to typically have substantial attrition [26]. For this reason, our primary outcome analysis will prioritize analysis of the subjects who adhered to their group assignment and were sufficiently exposed to the intervention. Therefore, both pre-protocol analysis (as treated analysis) as well as intention to treat analysis will be done and both results will be reported. The approach of conducting both “intention to treat analysis” together with “as treated analysis” has been observed in literature for example, Weinstein and colleagues [33] followed this approach in their randomized trial comparing surgical versus nonoperative treatment for lumbar disk herniation.

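### The primary outcome analysis ranks adherent, exposed participants ahead of intention to treat, for a reason (attrition) that does not support it

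*Protocol article*

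**What the plan says.** In the protocol article, the section on the primary outcome (HIV Risk Perception Score) first observes that "it is common for eHealth trials to typically have substantial attrition". On that ground it states that "our primary outcome analysis will prioritize analysis of the subjects who adhered to their group assignment and were sufficiently exposed to the intervention". The next sentence commits to "both pre-protocol analysis (as treated analysis) as well as intention to treat analysis will be done and both results will be reported".

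The abstract's Methods paragraph gives no order: "We will conduct both intention to treat and as treated analysis". No section makes intention to treat the primary analysis.

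Two other sections determine whom the filter can remove:
- Description of the Intervention says of wait-list participants that they complete the same measures "but will not play the game until the post-intervention assessment".
- Four-Weeks Follow-Up Data Collection says that the game sends log data to the study servers and that "this will allow us to assess the exposure to the intervention". Exposure is therefore known only after randomisation.

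**The concern.** Hypothesis 1 is a superiority claim about the change in risk perception between randomised arms. Three features of the stated priority weaken that comparison.

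- **The reason does not lead to the choice.** Attrition means missing 4-week scores. Dropping people who did not adhere or played too little restores none of those scores and removes further participants.
- **The selection is uneven between arms.** Only intervention participants have an amount of play to reach. The prioritised comparison sets self-selected players against controls who faced no such test, and randomisation does not protect it. Participants know their arm and report the outcome themselves, so a link between engagement and score movement is plausible.
- **The prioritised set is ambiguous.** Per-protocol drops people who deviate; as-treated regroups them by what they received. A control who played the game is removed under one and counted as treated under the other.

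If the two analyses disagree, the plan as written leads with the one that randomisation does not protect.

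**Working it through.** **1. The plan's own figure.** Inputs from Sample Size Calculation: difference 0.477, SD 1.03, two-sided alpha 0.05, power 80%, allocation 1:1.

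n per arm = 2 × [1.03 × (1.960 + 0.842) / 0.477]² = 73.2.

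The stated 73 is this value rounded down, and power at 73 per arm is 79.9%. The planned difference is 0.477 / 1.03 = 0.463 SD. The figure reproduces when 0.477 is a raw difference on the SD of 1.03.

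**2. Completers.** 380 randomised with the plan's 30% loss gives 380 × 0.7 = 266, or 133 per arm.

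**3. Selection with no true effect.** Let engagement be standard normal with correlation r to the change in score. Keep the most engaged fraction f of the intervention arm and all controls. The document gives neither r nor f; both are assumptions.

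- Bias in SD units = r × φ(k) / f, with k the cut-off that keeps fraction f. The multiplier φ(k) / f is 0.350 at f = 0.8, 0.497 at 0.7, 0.644 at 0.6 and 0.798 at 0.5.
- SE in SD units = √[1/(133f) + 1/133], which gives 0.130, 0.135, 0.142 and 0.150 for the same f.
- Two-sided type I error = Φ(−1.96 − bias/SE) + 1 − Φ(1.96 − bias/SE).

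Each cell shows bias in SD units, then type I error:

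| r | f = 0.8 | f = 0.7 | f = 0.6 | f = 0.5 |
|---|---|---|---|---|
| 0 | 0; 5% | 0; 5% | 0; 5% | 0; 5% |
| 0.1 | 0.04; 6% | 0.05; 7% | 0.06; 7% | 0.08; 8% |
| 0.2 | 0.07; 8% | 0.10; 11% | 0.13; 15% | 0.16; 19% |
| 0.3 | 0.11; 13% | 0.15; 20% | 0.19; 28% | 0.24; 36% |

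A simulation with 5,000 runs per case at f = 0.8, 0.6 and 0.5 agrees to within about one percentage point (for example 35.8% at r = 0.3, f = 0.5). Intention to treat stayed at about 5% in every case. The largest bias, 0.24 SD or 0.247 on the raw scale, is 0.247 / 0.477 = 52% of the planned difference. A negative r gives the same sizes with the sign reversed, so the bias then runs against the game.

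**4. Power if intention to treat is primary.** With 133 per arm, SE = 1.03 × √(2/133) = 0.126. Take 0.477 as the effect in those exposed and assume that the unexposed gain nothing. The diluted effect is 0.477 × f and power = Φ(0.477f / 0.126 − 1.96).

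| Exposed share f | Diluted effect | Power |
|---|---|---|
| 1.0 | 0.477 | 96.5% |
| 0.8 | 0.382 | 85.6% |
| 0.7 | 0.334 | 75.3% |
| 0.6 | 0.286 | 62.0% |
| 0.5 | 0.239 | 47.1% |

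**The case against.** The strongest reply is that intention to treat is already planned: the section says "as well as intention to treat analysis will be done and both results will be reported". On a softer reading, the sentence about priority only explains why an adherence analysis is added. That limits the defect to one of rank, since nothing is omitted. It does not remove it, because the sentence names the primary outcome analysis and no other text puts intention to treat first.

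A reader might go further in four ways that the document does not support.

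- **That only intervention participants can be removed.** This is true of the exposure condition alone. The game is offered through the website, the Google Play store, cellular shops and kiosks, so a control who obtained it could fail the adherence condition. How often depends on the unlock code.
- **That the bias favours the game.** More engaged players might already be well informed and have less room for their score to rise. Neither the sign nor the size of the correlation is given, and at zero correlation there is no bias.
- **That a null intention-to-treat result would be presented as positive.** This is conjecture about reporting, and the plan commits to showing both results.
- **That the click-through rule is part of the same fault.** Data Quality Assurance says that "inconsistent records will be documented and censored from the final analysis". This is a plausibility check applied to both arms, with a blinded analysis team, and nothing shows that it would act unevenly. Whether to keep such records is a debatable preference and no change is asked for.

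The lack of a numerical exposure threshold is also not counted here. An article commonly leaves that detail to the full protocol or analysis plan.

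**Conclusion.** The concern holds as a fault of priority. Current text puts a set selected after randomisation ahead of intention to treat for the primary outcome of a superiority trial, and the reason it gives does not support doing so. It also merges two different analysis sets under one name.

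The possible size runs from nothing to serious: type I error of 5% at zero correlation, 6 to 8% at 0.1, 8 to 19% at 0.2 and 13 to 36% at 0.3, for 80% down to 50% exposed. These figures rest on the assumed correlations and exposure shares, on 133 completers per arm, and on exposure selection in the intervention arm only. They show what the rule permits and do not predict this trial's bias, whose direction remains open. Because the rule governs the headline result and the article describes the study as not yet started, it should be corrected before data are seen.

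**What to change.** State that intention to treat, with all randomised participants analysed by assigned arm, is the single primary analysis on which hypothesis 1 is decided. Label the adherence-based analysis secondary and supportive, and call it either per-protocol or as-treated according to which is meant. Remove attrition as the justification. Intention to treat does not by itself repair missing 4-week scores, so their handling is a separate matter that the analysis plan can set out.

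The change is one of wording, and the sample size stays at 380. The statistical cost is dilution by non-players. If they gain nothing, power stays above the planned 80% at 80% exposed but falls below it at 70% (75%) and to 47% at 50%. The sponsor should accept this knowingly, since it depends on how many participants play the game.

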## Methods

### Study Design and Hypotheses

The Swaziland Serious Games–Based HIV Prevention Trial (SGprev trial) will be a 4-week, two-arm randomized intervention trial. Participants will be randomized into 2 groups (the intervention group and a wait-list control group) in a 1:1 allocation ratio (Figure 1) [18]. The intervention will be downloadable from our website, on the Google Play store, and in popular cellular shops around Swaziland. These cellular shops already serve as distribution sites for other mobile software and apps, such as antiviruses, Opera mini, and WhatsApp, and are thus very popular in Swaziland. Additionally, the game will also be available from kiosks in all tertiary institutions in the country. Downloading the game will not be synonymous with enrolling in the trial. After downloading the game, potential participants will be redirected or prompted to visit our website where information about the trial and eligibility screening will be provided.

We plan to test whether a serious game intervention delivered on mobile phones to increase HIV risk perception, increases the intention to reduce multiple sexual partnerships, intention to know own HIV status, and intention to know all sexual partners’ HIV status will be more effective compared with current prevention efforts. Therefore, our hypotheses are that

1. The change in HIV risk perception between pre- and post-intervention assessment is greater in the intervention group compared with the change in the control group.

2. The change in HIV risk perception between pre- and post-intervention assessment will be greater among those reporting high HIV risk behavior in the intervention group compared with the control group.

3. The change in intention to have an HIV test between pre- and post-intervention assessment will be greater in the intervention group compared with the change in the control group.

4. The change in intention to reduce multiple concurrent partnerships between pre- and post-intervention assessment will be greater in the intervention group compared with the change in the control group.

5. The intervention group will report higher rate of condom use in the last sexual encounter compared with the control group.

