### Sample Size Calculation

The trial will be powered on the primary outcome measure and based on comparison of the change in HIV risk perception score from pre- to post-intervention assessment in the intervention group at 4 weeks. A study conducted in Uganda estimated mean HIV risk perception of M=3.27, SD *=* 1.03, therefore, we used this estimation as our baseline mean and SD to calculate our effect size [21]. Assuming a moderate effect size of 0.477 (identified by Chu et al [22]), alpha (two-tailed)=0.05, beta=0.20, with 1:1 allocation ratio between both groups, and a SD of the outcome in the population of 1.03, the total sample required to sufficiently power the study would be 146 (73 for each group). Moreover, assuming a 30% loss to follow-up rate [15], we then inflated the sample by 30% to yield a sample of 190. After that, we considered gender differences and once more inflated the sample by a factor of 2 to give a final sample size of 380. Finally, to ensure a balance between males and females in both groups we will recruit 190 females and 190 males. The sample size was calculated using Web-based sample size calculation software [23,24].

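### The non-ITT analysis of the primary outcome is described as a per-protocol set but labelled as treated, and the two labels give different datasets for the analysis the plan puts first

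*Protocol article*

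**What the plan says.** Three statements in the protocol article bear on this.

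- **Description of the set** (Primary Outcome Measure: HIV Risk Perception Score, under Data Management and Statistical Analysis): "our primary outcome analysis will prioritize analysis of the subjects who adhered to their group assignment and were sufficiently exposed to the intervention".
- **Label, next sentence of the same section:** "both pre-protocol analysis (as treated analysis) as well as intention to treat analysis will be done and both results will be reported". I read *pre-protocol* as a slip for *per-protocol*. The section then cites a randomised trial of surgical versus nonoperative treatment as a precedent for reporting intention to treat together with as treated.
- **Label in the abstract, Methods:** "We will conduct both intention to treat and as treated analysis". Per-protocol is not mentioned there.

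The article does not say whether a game-arm participant who does not play, or a control who does, is excluded or counted in the other group.

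Other sections bear on how often such participants may occur. Log data are collected and "this will allow us to assess the exposure to the intervention" (Four-Weeks Follow-Up Data Collection). Controls "will not play the game until the post-intervention assessment" (Description of the Intervention). However, "The intervention will be downloadable from our website, on the Google Play store, and in popular cellular shops around Swaziland" (Study Design and Hypotheses). The Randomization section mentions a game unlock code.

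**The concern.** Per-protocol and as treated are different analyses. Per-protocol keeps people in their randomised arm and drops those who did not follow it. As treated normally drops nobody on grounds of adherence and groups people by what they actually did. A game-arm non-player is absent from the first dataset and sits in the comparison group of the second. A control who plays is absent from the first and sits in the game group of the second.

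An analyst working from the abstract and one working from the description in the statistical section would build different datasets from the same data. The plan gives this set priority for the primary outcome, so the ambiguity reaches the headline result. Exposure is self-directed and participants are not blinded, so those who play may well differ from those who do not in how their risk perception moves. In that case both analyses are biased, as treated more so.

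**Working it through.** **1. Inputs from the plan.** The plan gives no figure for this point, so only its sample-size inputs can be reused: "alpha (two-tailed)=0.05, beta=0.20, with 1:1 allocation ratio between both groups", effect 0.477, SD 1.03, 30% loss, final N 380. Its calculation reproduces when 0.477 is read in scale points:

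n per arm = 2 × (1.960 + 0.842)² × 1.03² / 0.477² = 73.2

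That is 74 per arm rounded up, against the stated 73; power at 73 per arm is 0.799. Then 146 × 1.3 = 190 and 190 × 2 = 380. After 30% loss, 380 × 0.70 / 2 = 133 are analysed per arm.

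**2. Assumptions, not in the documents.**

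- A share e of the game arm is insufficiently exposed.
- A share c of controls plays, all of them engaged people.
- Engaged people (share 1 − e in both arms) change by s points more than the unengaged, whatever the game does.
- SD 1.03 applies to the change score.
- The game has no effect.

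**3. Bias.** Players all belong to the engaged group, so their mean is s above the unengaged.

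- Per-protocol comparator: controls who did not play, mean (1 − e − c)s / (1 − c).
- As-treated comparator: the same controls plus game-arm non-players, mean (1 − e − c)s / (1 − c + e).

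With c = 0 the biases reduce to e·s and 2e·s/(1 + e). At e = 0.3, s = 0.3:

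- c = 0, per-protocol: 0.3 × 0.3 = 0.09
- c = 0, as treated: 2 × 0.3 × 0.3 / 1.3 = 0.138
- c = 0.1, per-protocol: 0.3 − 0.6 × 0.3 / 0.9 = 0.10
- c = 0.1, as treated: 0.3 − 0.6 × 0.3 / 1.2 = 0.15

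**4. Type I error.** SE = 1.03 × √(1/n₁ + 1/n₂), and the two-sided rejection probability follows from z = bias/SE.

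| Case | n₁, n₂ | SE | z | Type I error |
|---|---|---|---|---|
| c = 0, per-protocol | 93.1, 133 | 0.139 | 0.65 | 10% |
| c = 0, as treated | 93.1, 172.9 | 0.132 | 1.05 | 18% |
| c = 0.1, per-protocol | 93.1, 119.7 | 0.142 | 0.70 | 11% |
| c = 0.1, as treated | 106.4, 159.6 | 0.129 | 1.16 | 21% |

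Simulation (4,000 runs) agrees: 10%, 18%, 11% and 22%. Intention to treat stays at 5%.

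**5. Sensitivity to the assumptions.**

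- *Better adherence.* At e = 0.1, c = 0, s = 0.3 the biases are 0.03 and 0.055, and type I error is about 6% against 7%.
- *Different selection model.* Let a continuous trait drive both playing and change, with correlation b between trait and change. With 10% non-players and no control play, b = 0.2 gives 6% against 9%. With 30% and 10%, b = 0.2 gives 18% against 42%, and b = 0.3 gives 34% against 75%.
- *No link between engagement and change* (b = 0), or full adherence: all analyses stay at about 5% with no bias.
- *A real effect* of 0.477 in players, with e = 0.3, c = 0.1, s = 0.3: per-protocol 0.477 + 0.10 = 0.58, as treated 0.477 + 0.15 = 0.63, intention to treat 0.477 × (0.7 − 0.1) = 0.29.

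**The case against.** The strongest reply is that the statistical section gives only one working description, "analysis of the subjects who adhered to their group assignment and were sufficiently exposed to the intervention", and that the following sentence merely names that set. On this reading the plan has a per-protocol set with a wrong label. That largely stands. A reader might infer that the plan lays down two full set definitions, or that it intends to move non-players into the control group. The documents do not support either: no sentence states a reclassification rule, and that rule comes only from the usual meaning of the label. Nor do the two labels put the same person in opposite arms, since per-protocol excludes where as treated moves.

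A reader might also take the cited surgical trial as evidence that reclassification is meant. The article cites it for the practice of reporting two analyses and does not say how its patients were classified, so it cannot carry that weight.

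Three further points have force. The sizes depend wholly on assumed adherence and selection, and the two models differ widely. The 10% control play has to be weighed against the rule that controls wait and against the unlock code, although public download leaves a route open. And intention to treat is also to be reported, so an analysis at the 5% level is always visible, which limits selective reporting.

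What the reply does not remove is that the abstract names only the other analysis and the statistical section equates the two. Detailed rules, such as the exposure threshold, may be left to an analysis plan that is not shown, and their absence is not counted here. Conflicting names for a prioritised analysis are a different matter.

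**Conclusion.** The point holds as an inconsistency of label and description. The set is described as per-protocol, called as treated in the same section, and called only as treated in the abstract. It matters because the plan prioritises this analysis for the primary outcome.

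In the working's base illustration, the as-treated reading adds about 0.05 points of bias to per-protocol and roughly doubles its type I error. This requires non-adherence that is related to change in risk perception; the documents neither establish nor exclude that. Most of the departure from intention to treat in that illustration (0.09 to 0.10 points) belongs to per-protocol itself and would survive a correction of the label alone. That is why the order of the analyses has to be corrected along with the name.

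**What to change.** - In the abstract and in the primary outcome section, replace *as treated* and *pre-protocol* with *per-protocol*.
- Add one sentence: each participant is analysed in the randomised arm or excluded, and is never moved to the other arm. Game-arm participants who were not sufficiently exposed and controls who played are excluded.
- Keep the surgical trial, if at all, only as a precedent for reporting two analyses.
- Change the sentence that prioritises the adherent set, so that intention to treat is primary and the per-protocol set is supportive and reported beside it.

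The cost is wording in two places, while the study is still at the pre-initiation stage. The per-protocol set is somewhat smaller than an as-treated one: in the illustration with 10% control play, about 93 + 120 = 213 against 106 + 160 = 266. Per-protocol still carries some selection bias, so it should be read with that in mind.
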